### Objectives and hypotheses

1.2.

This trial aims to evaluate the feasibility of a placebo-controlled study of single-dose psilocybin in the treatment of OCD, to evaluate safety and tolerability, to provide initial evidence as to the effects of oral psilocybin on OCD symptomatology, as well as provide initial data on the neural mechanisms that may mediate psilocybin’s purported therapeutic effects on OCD.

To do so, we will use a randomized, double-blind, niacin placebo-controlled, non-crossover study design, coupled with pre-post-dosing fMRI. The choice of a single dose – as opposed to multiple administrations, as in Moreno et al. (35) – was balanced with considerations of the addition of a neuroimaging component with repeat scanning, an increase in target sample size, the use of a randomized controlled design, available budget, and the need to focus our research questions.

To investigate the effects of oral psilocybin compared to placebo on OCD symptom severity, we set the primary endpoint as 48 h post-dosing. This endpoint was selected to mitigate the possibility of sleep difficulties the night of dosing interfering with ratings and scans the next day. We hypothesize that psilocybin will lead to greater OCD symptom improvement than placebo at 48 h post-dosing. We will also track safety, tolerability, and feasibility metrics throughout the study. Additionally, we will explore the interrelationships among psilocybin-induced changes in resting-state brain connectivity and OCD symptoms. Several studies indicate that abnormal frontostriatal connectivity is central to the pathophysiology of OCD, and these regions are also affected by psilocybin. We hypothesize that at 48 h post-dosing, compared to placebo: (a) psilocybin will normalize abnormal frontostriatal functional connectivity in patients with OCD; and (b) normalization of frontostriatal functional connectivity will correlate with improvement in OCD symptomatology after psilocybin dosing. Lastly, to explore effects on constructs beyond OCD, we will examine differences between psilocybin and placebo in changes on various secondary symptom and personality measures from baseline to 48 h post-dosing.

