#### Neuroimaging

2.3.6.

In the randomized phase, neuroimaging will be conducted at baseline 24 h pre-dosing and 48 h post-dosing. At these intervals, study personnel will accompany participants to the MRRC, where technologists will review participants’ responses on the MRI Safety Questionnaire, obtain signed informed consent for the day’s neuroimaging procedures, and conduct additional screening and safety determination if necessary (e.g., X-ray to rule out embedded metal in case of recent exposure).

MRI acquisition will be conducted using a Siemens 3 Tesla MRI scanner. Using a 64-channel head coil, the scan protocol will begin with a 3-plane localizer, scout image, and aligned 3-plane localizer that will serve as a localization series for the other acquisitions. The remaining multimodal MR pulse sequences will include: high resolution T1-weighted imaging (i.e., MPRAGE); high resolution T2-weighted imaging; spin echo field maps acquired in opposing phase encoding directions prior to each fMRI session; multi-band BOLD gradient echo planar imaging at rest; diffusion weighted imaging (DWI), and arterial spin labeling (ASL). The T1 and T2 acquisitions are set to use an “Adjust Volume” that matches the size and positioning of the spin echo field maps and resting state fMRI scans. Total MR acquisition may last between 1.5 and 2 h depending on whether some series must be re-acquired due to confounds/artifacts.

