##### Secondary outcome

2.4.1.2.

The secondary outcome in this study is resting-state brain connectivity, which will be assessed at baseline and 48 h post-dosing.

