### Statistical analysis

2.9.

We will conduct linear mixed modeling (LMM) with restricted maximum likelihood estimation (to handle missing data) with appropriate alpha correction in SPSS to test our first hypothesis that psilocybin, compared to placebo, will improve OCD symptoms at the primary endpoint of 48 h post-dosing on the VAS for OCD symptoms and AY-BOCS. Treatment, time, and all interactions will be modeled as fixed effects. Participants will be modeled as a random effect. The time factor will be specified as baseline to 48 h post-dosing. Alpha-corrected *t*-tests will be used to probe interaction effects.

MRI preprocessing and group difference statistics will be evaluated using standard regression and general linear modeling approaches in a general-purpose MRI analysis package (QuNex), a processing platform that incorporates several state-of-the art neuroimaging tools (FSL, FreeSurfer, AFNI, SPM, PALM, and HCP-MPP) and thus offers comprehensive multimodal MRI analytic capabilities (92). To test the secondary hypothesis that at 48 h post-dosing, psilocybin, compared to placebo, will normalize frontostriatal connectivity at rest, we will conduct similar LMMs to examine the effect of psilocybin on activation of the corresponding regions. To test the secondary hypothesis that normalization of activity in these regions at 48 h post-dosing will correlate with clinical improvement in OCD symptoms (i.e., on the VAS for OCD symptoms, AY-BOCS, and Y-BOCS), we will conduct a correlational analysis with these variables.

Exploratory analyses of change in other secondary outcomes from baseline to 48 h post-dosing will be conducted using similar LMMs. Safety data will be presented as descriptive statistics. Data from the one-month post-dosing interviews will be qualitatively analyzed *via* interpretative phenomenological analysis (IPA) (93).

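### The imaging hypotheses and secondary outcome are about frontostriatal connectivity, but Section 2.9 names regional activation and activity as the variables to be analysed

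*Protocol article*

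**What the plan says.** Section 1.2 of the protocol article sets two imaging hypotheses for 48 h after dosing, each against placebo. The first is that "psilocybin will normalize abnormal frontostriatal functional connectivity in patients with OCD". The second is that "normalization of frontostriatal functional connectivity will correlate with improvement in OCD symptomatology after psilocybin dosing". Section 2.4.1.2 agrees with both: "The secondary outcome in this study is resting-state brain connectivity", measured at baseline and at 48 h.

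Section 2.9 gives the tests. It introduces the first hypothesis in the same terms, that "psilocybin, compared to placebo, will normalize frontostriatal connectivity at rest", and then closes the sentence with "we will conduct similar LMMs to examine the effect of psilocybin on activation of the corresponding regions". It restates the second hypothesis as "normalization of activity in these regions at 48 h post-dosing will correlate with clinical improvement in OCD symptoms", to be examined by a correlational analysis.

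Two other places bear on the reading. Section 2.3.6 lists "multi-band BOLD gradient echo planar imaging at rest" among the scans, together with arterial spin labeling, and mentions no task. Section 2.2 describes the functional connectivity analyses as largely exploratory.

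**The concern.** The dependent variable named in the analysis section is not the one named in the hypotheses and the outcome. Connectivity describes how the signals of two regions vary together. Activation or activity describes the signal within one region. A mixed model on the second does not answer a question about the first.

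The stake is interpretive. An analyst who follows Section 2.9 to the letter would report regional signal and would have no result for the declared secondary outcome. An analyst who follows Sections 1.2 and 2.4.1.2 would report connectivity and would depart from the written analysis. Either could claim to have followed the article, so the choice of variable could be questioned once results are known.

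A smaller, related matter is the word normalize. The comparison is between two arms of patients with OCD, so it shows a difference in change. Whether that change is toward normal needs something further.

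**Working it through.** The article gives no figure on this point, so the check is mainly a comparison of text, with a short demonstration that the two quantities are separable.

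**Step 1. Set the passages side by side.**

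| Item | Sections 1.2 and 2.4.1.2 | Section 2.9, hypothesis as restated | Section 2.9, variable analysed |
|---|---|---|---|
| First hypothesis | frontostriatal functional connectivity | frontostriatal connectivity | activation of regions |
| Second hypothesis | frontostriatal functional connectivity | activity in regions | activity in regions |
| Secondary outcome | resting-state connectivity | – | – |

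The shift occurs for both hypotheses. For the first, it happens within a single sentence.

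**Step 2. Does the article treat the terms as interchangeable?** It does not. Section 1.1 reports decreases in regional BOLD signal and cerebral blood flow under psilocybin, and reports reduced coupling between posterior cingulate and medial prefrontal cortex as the result of a further, seed-based analysis.

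**Step 3. Could a regional analysis be run on the planned data?** Yes. Section 2.3.6 acquires arterial spin labeling, a perfusion measure, as well as resting BOLD. The absence of a task therefore does not rule out a literal reading of Section 2.9.

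**Step 4. Are the quantities separable?** For two regional signals X and Y, connectivity as a correlation is r = cov(X, Y) / (SD_X × SD_Y). The regional summaries are the mean and SD of each signal alone. The settings below are illustrative and are not trial data. Each row was also simulated with 200,000 draws.

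| Setting | cov / (SD × SD) | Simulated regional means | Simulated regional SDs | Simulated r |
|---|---|---|---|---|
| SD 1.0, r 0.6 | 0.6 / 1.0 = 0.6 | 0.004, 0.001 | 0.997, 0.999 | 0.600 |
| SD 1.0, r 0.2 | 0.2 / 1.0 = 0.2 | −0.002, −0.003 | 0.998, 1.000 | 0.200 |
| SD 1.5, r 0.6 | 1.35 / 2.25 = 0.6 | −0.000, 0.004 | 1.499, 1.500 | 0.601 |

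Rows 1 and 2 show coupling falling from 0.6 to 0.2 with regional mean and SD unchanged. Rows 1 and 3 show amplitude rising by half with coupling unchanged. A test on one quantity is therefore not a test on the other.

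**Step 5. What can the arm contrast show?** Section 2.2 recruits only people with OCD, and Section 2.1 randomises them to psilocybin or niacin. The treatment-by-time term estimates how much more one arm changed than the other. Reading that as movement toward normal needs a reference value or an expected direction. Section 1.1 gives a direction for regional activity, calling several regions hyperactive in OCD. For frontostriatal connectivity the article says only that it is abnormal.

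**The case against.** The best defence is that this is loose wording in a condensed article. The sentence in Section 2.9 opens with connectivity, Section 2.2 speaks of functional connectivity analyses, and Section 2.4.1.2 names connectivity as the outcome. A sympathetic reader would guess that connectivity will be analysed. That is plausible, and it means nobody can say from the article that the wrong analysis will be run. It does not remove the contradiction. The substitution appears for both hypotheses, in the section that specifies the tests, and Section 1.1 keeps the two ideas apart. The article has not left the variable to another document; it has named one that conflicts with its own outcome.

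Three stronger readings are tempting, and the documents do not support them.

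- A reader might infer that normalization cannot be assessed at all because there is no healthy arm. A normative dataset, the regions and a working definition may sit in the full protocol or analysis plan, which are not shown. What can be said is that the article itself supplies none for frontostriatal connectivity.
- A reader might infer that the planned test has power equal only to its significance level, 5%. That holds only if connectivity changes while regional signal does not change at all. Step 4 shows that this can happen in principle. Nothing in the article says it will happen here.
- A reader might infer that the mixed model should give way to a baseline-adjusted analysis of a transformed correlation. Those are preferences. The treatment-by-time model in Section 2.9 is not shown to be wrong.

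**Conclusion.** The inconsistency is real and lies within the article. Both imaging hypotheses and the sole secondary outcome are stated as connectivity, while the analysis section names regional activation for one hypothesis and regional activity for the other. As worded, the analysis does not test what was hypothesised.

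The weight is moderate to low. The outcome is secondary and the analyses are described as largely exploratory. The primary efficacy and safety analyses, the sample size, the randomisation and the scan acquisition are unaffected. No numerical size can be attached, because the consequence depends on which variable is eventually analysed and on how far regional signal and coupling move together in these patients, which the documents do not say.

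The conclusion rests on giving activation and activity their ordinary meaning, which is how Section 1.1 uses activity. If the full protocol already names connectivity as the analysed variable, what remains is an error of wording in the article that still needs correcting.

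**What to change.** Make two changes in Section 2.9 and one in how the result is described.

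1. In the sentence on the first hypothesis, name frontostriatal resting-state functional connectivity as the dependent variable of the mixed model. Keep the treatment, time and interaction terms as they stand.
2. In the sentence on the second hypothesis, replace regional activity with the change in that same connectivity measure, and correlate this change with symptom improvement.
3. Report the arm contrast as change in connectivity relative to placebo. Use normalization, in Sections 1.2 and 2.9 and in the results, only if a reference or an expected direction for frontostriatal connectivity has been specified before the imaging data are analysed.

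If a regional analysis of activity or perfusion is also wanted, list it separately as exploratory.

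The cost is wording only: no added scan, visit or participant. The claim becomes slightly more modest unless a reference or direction is supplied. Making the change before the imaging data are analysed avoids any suggestion that the variable was chosen after the fact.

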#### Unblinding

2.3.8.

Participant and facilitator blinding are maintained only until the primary endpoint of 48 h post-dosing in the randomized phase, to facilitate scheduling of subsequent open-label dosing for participants assigned to placebo (see Section 2.3.10.1). Specifically, unblinding will occur at the start of the 48 h post-dosing integration visit, which will always occur after the 48 h post-dosing ratings and fMRI scan. Independent raters will remain blinded until after the one-week post-dosing ratings are completed, which will be past the primary endpoint, thus not impacting primary outcomes.

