##### Primary outcomes

2.4.1.1.

The primary outcome measures are the acute version of the clinician-administered Y-BOCS (AY-BOCS) (52) and the self-report Visual Analog Scale (VAS) for OCD symptoms (53), both of which assess OCD symptom severity over the past 24 h. These will be administered by independent raters at baseline and 24 and 48 h post-dosing. The Y-BOCS will also be administered by the same raters at baseline and 1, 2, 4, 8, and 12 weeks post-dosing.

Safety outcomes are included as primary outcomes as well. Safety measures assessed only during dosing include vitals and SUDs, and those assessed throughout the study duration include the Since Last Visit version of the C-SSRS (54), AEs, and any required changes to psychiatric or non-psychiatric medication regimens. The Since Last Visit version of the C-SSRS (54) assesses suicidal ideation severity, ideation intensity, and suicidal behavior severity (including non-suicidal, self-injurious behaviors) since the last assessment interval (i.e., the last study visit). AEs are defined as any untoward physical, social, economic, or psychological occurrence affecting participants, including any abnormal laboratory finding, symptom, reaction, or disease. An AE does not necessarily have a causal relationship with study procedures, and are graded as mild, moderate, or severe in this study. Severity of an AE is considered distinct from its “seriousness.” An AE is considered serious (i.e., SAE) if it: (1) is life-threatening; (2) results in hospitalization, disability/incapacity, a congenital anomaly or birth defect, or death; (3) requires medical or surgical intervention to prevent aforementioned outcomes; or (4) adversely affects the risk/benefit ratio of the study. Therefore, a severe AE is not necessarily an SAE.

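### The 48 h brain–symptom test names the Y-BOCS, which has no 48 h value and is first taken after participants are unblinded; how arm enters the correlation is left open

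*Protocol article*

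**What the plan says.** All references are to the protocol article.

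- **Hypothesis (section 1.2).** The connectivity hypotheses share one lead-in: "We hypothesize that at 48 h post-dosing, compared to placebo". Part (b) under it reads "normalization of frontostriatal functional connectivity will correlate with improvement in OCD symptomatology after psilocybin dosing".
- **Test (section 2.9).** The hypothesis is restated as "normalization of activity in these regions at 48 h post-dosing will correlate with clinical improvement in OCD symptoms". Improvement is then defined and the method given: "i.e., on the VAS for OCD symptoms, AY-BOCS, and Y-BOCS), we will conduct a correlational analysis with these variables". The article names no Y-BOCS visit, analysis population or arm term.
- **Symptom schedule (section 2.4.1.1).** For the AY-BOCS and VAS: "These will be administered by independent raters at baseline and 24 and 48 h post-dosing". For the standard Y-BOCS: "The Y-BOCS will also be administered by the same raters at baseline and 1, 2, 4, 8, and 12 weeks post-dosing".
- **Connectivity schedule (section 2.4.1.2).** "The secondary outcome in this study is resting-state brain connectivity, which will be assessed at baseline and 48 h post-dosing".
- **Blinding (section 2.3.8).** For participants and facilitators, "unblinding will occur at the start of the 48 h post-dosing integration visit", after the 48 h ratings and scan. Independent raters stay blind until the 1-week ratings are done.
- **Open-label phase (section 2.3.10.1).** Placebo participants may receive psilocybin about 2 weeks after unblinding.

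**The concern.** One of the three symptom measures named for the 48 h test has no value at 48 h. Anyone programming section 2.9 must either leave that correlation out or choose one of five later Y-BOCS visits. The article does not say which, and each of the five follows participant unblinding. Section 2.3.8 justifies early unblinding on the ground that the primary outcomes are already collected. That reasoning does not cover a secondary-hypothesis test that uses later Y-BOCS scores.

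The second issue is the form of the test. The hypothesis is framed against placebo, but the method named is only a correlation. If psilocybin moves both connectivity and symptoms, a correlation over both arms combined will show an association even when the two are unrelated among participants given the same treatment. A common treatment effect could then be read as a brain–symptom link. This is the only planned analysis that connects brain change to symptom change, so its meaning should be fixed in advance.

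**Working it through.** **1. Timing.** The article gives no sample size, power or expected r for this correlation, so there is no figure to reproduce. The check is to set the schedules side by side.

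| Measure | Baseline | 24 h | 48 h | 1 week | 2, 4, 8, 12 weeks |
|---|---|---|---|---|---|
| Connectivity | yes | – | yes | – | – |
| AY-BOCS, VAS | yes | yes | yes | – | – |
| Y-BOCS | yes | – | – | yes | yes |
| Participant blind at rating | yes | yes | yes | no | no |
| Rater blind at rating | yes | yes | yes | yes | not protected |

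The first post-dose Y-BOCS is at 7 × 24 = 168 h, which is 168 − 48 = 120 h after the scan. A baseline-to-48 h Y-BOCS change does not exist.

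**2. Later Y-BOCS visits.** Unblinding on day 2 plus about 14 days puts open-label dosing at about day 16 after blinded dosing. For placebo participants who accept it, the 4-, 8- and 12-week points (days 28, 56 and 84) would follow active drug. The 2-week point (day 14) falls only just before. The 1-week visit is the only post-dose Y-BOCS clearly ahead of open-label dosing and still rated blind.

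**3. What arm handling could do.** Inputs from section 2.2: projected symptom d = 1.5; 30 completers at 1:1, so 15 per arm; two-sided α = 0.05; connectivity d of 0.2 to 0.3 cited from a placebo-controlled study in healthy controls. Larger connectivity effects are assumed here, because the article speculates that effects may be greater in patients. Treating these values as between-arm standardized differences in change is also an assumption.

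With zero within-arm correlation and equal arms, the pooled correlation is

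r = (d_s·d_c/4) / √[(1 + d_s²/4)(1 + d_c²/4)].

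For d_s = 1.5 and d_c = 0.3: 0.1125 / √(1.5625 × 1.0225) = 0.1125 / 1.264 = 0.089.
For d_s = d_c = 1.5: 0.5625 / 1.5625 = 0.36.

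Rejection rates come from 40,000 simulated trials of 15 per arm, with no within-arm association:

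| Connectivity d | Source | Pooled r | Pooled test | Adjusted for arm |
|---|---|---|---|---|
| 0.2 | protocol | 0.06 | 6.3% | 5.0% |
| 0.3 | protocol | 0.09 | 7.6% | 4.9% |
| 0.5 | assumed | 0.15 | 12.2% | 5.0% |
| 1.0 | assumed | 0.27 | 31.6% | 5.1% |
| 1.5 | assumed | 0.36 | 54.6% | 5.2% |

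**4. Precision of the alternatives.** By the Fisher z approximation, the r detectable with 80% power is tanh[(1.960 + 0.842)/√(n − 3)]. For n = 15 this is tanh(2.802/3.464) = 0.67. For n = 30 it is tanh(2.802/5.196) = 0.49.

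**The case against.** **Timing.** In section 2.9 the 48 h label is attached to the brain measure, and the improvement carries no time of its own. Relating 48 h connectivity to later improvement on the standard scale is a coherent analysis, and it can be computed from 1 week onward. Raters are still blind at 1 week. Within the psilocybin arm all participants have received the same allocation information, so unblinding adds no between-arm difference there. This stands as a possible reading of section 2.9. It does not agree with section 1.2, whose lead-in sets the hypothesis at 48 h, and it leaves the visit unnamed.

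**Arms.** A reader might infer that the plan pools the arms in one correlation and ignores treatment. The documents do not support that. The article states neither pooling nor separation, it names three symptom measures, and the wording of hypothesis (b) allows an analysis within the psilocybin arm. Analysis population and covariates are details that an article commonly leaves to the full protocol or analysis plan. This objection stands, and the arm issue is therefore only a conditional risk.

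**Size and importance.** A reader might take 55% as the expected error rate, or the correlation as the trial's only evidence on mechanism. Neither follows. The 55% needs a connectivity effect at least five times the cited range (1.5/0.3 = 5). The randomized comparison of connectivity under hypothesis (a) also bears on mechanism, and section 2.2 calls the connectivity analyses largely exploratory.

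**Conclusion.** The timing conflict is established from the text. Sections 1.2, 2.4.1.1 and 2.9 cannot all hold for the Y-BOCS: that correlation cannot test the 48 h hypothesis. At best it is a lagged association, 120 h or more after the scan, in participants who know their arm. From 4 weeks on it would also be affected by open-label psilocybin in placebo participants who take it.

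The arm issue is a conditional weakness. A plain correlation is an incomplete test of a hypothesis framed against placebo. If the arms were pooled without adjustment, the false-positive rate would be about 6% to 8% at the protocol's own connectivity effects, and about 12%, 32% and 55% at assumed d of 0.5, 1.0 and 1.5. These figures rest on symptom d = 1.5, 15 completers per arm, normal data and zero within-arm correlation. Adjusting for arm holds the rate near 5% throughout.

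The point concerns a secondary hypothesis. It does not touch the primary comparison of AY-BOCS and VAS at 48 h. It is worth correcting because the correction is cheap and removes a stated inconsistency.

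**What to change.** 1. Limit the 48 h brain–symptom test to baseline-to-48 h change in AY-BOCS and VAS, and align sections 1.2 and 2.9 accordingly.
2. Drop the Y-BOCS from this test. Alternatively, report only its 1-week value separately, labelled as a lagged association collected after participant unblinding with raters still blind.
3. Replace the plain correlation with a regression of symptom change on connectivity change, with arm in the model, in all 30 completers. Give the psilocybin-only estimate as supportive.

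**Cost.** Wording and one degree of freedom (27 residual instead of 28). No new visit or data are needed. The psilocybin-only estimate will be imprecise: with 15 participants it has 80% power only for r of about 0.67, so it should not carry the conclusion.
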